##### Safety

• Proportion of patients with relevant adverse events during the first three months following the start of oral anticoagulation. These events include the following: INR >4 or <1.5; need for vitamin K; bleeding episode; thromboembolic event; need for LMWH; acute myocardial infarction; acute stroke; and death from any cause.

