### Study procedures

The various study visits will be distributed as shown in Table
1:

**Table 1 T1:** Study timeline

**Day**	**−3 or −2**	**0**	**3**	**7 (±1)**	**15 (±3)**	**30 (±5)**	**60 (±7)**	**90 (±7)**
Recruitment	**√**							
Informed consent	**√**							
Selection criteria	**√**							
Medical history	**√**							
Physical examination	**√**							**√**
Blood samples for pharmacogenetics	**√**							
Randomization	**√**							
Acenocoumarol dosing (initiation/adjustment)^a^		**√**	**√**	**√**	**√**	**√**	**√**	**√**
INR determination		**√**	**√**	**√**	**√**	**√**	**√**	**√**
Evaluation of side effects		**√**	**√**	**√**	**√**	**√**	**√**	**√**

^a^In order to perform appropriate dose adjustments, additional visits can be scheduled as needed, at the discretion of the clinical researcher.

Preselection phase: The patients with VTE will be identified in the emergency department or hospital ward within the first 48 hours of the VTE diagnosis (PTE and/or DVT) and will be checked to ensure they meet the selection criteria.

Before any specific study procedure is performed, the patient will receive the information verbally and in writing through the patient information sheet. The patient must consent to participation in the study in writing (two copies). The patient will keep a copy of the information sheet and the informed consent once they have been signed. Once patients have been included in the study, the medical monitor will be informed of their inclusion and the randomization envelope will be opened to determine the study group to which they will belong.

Patients who were considered for inclusion but were not admitted to the study will be registered in a patient-log along with the cause for their non-inclusion (lack of informed consent, selection criteria, practical issues, and so on).

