Days 3 and 7 ± 1: The INR will be determined (capillary blood sample analyzed with a portable coagulometer) in both groups, and the acenocoumarol dosage will be adjusted if necessary. Control group patients will follow the dosage indications according to the standard clinical practice and visits will be scheduled for day 3, day 7 ± 1 and day 15 ± 3, depending on the length of the hospital stay. Patients included in the intervention group will have their acenocoumarol regimen readjusted according to the developed algorithm and will be scheduled for visits on day 3, 7 ± 1 and 15 ± 3, depending on the length of the hospital stay.

INR measurements will be performed on both groups and additional visits deemed appropriate for good control of the anticoagulation will be arranged. Any changes made to the dosage and all INR measurements will be recorded in the CRF and the medical records.

Visit days 15 ± 3, 30 ± 5, 60 ± 7 and 90 ± 7: During each visit, and after determining the INR (capillary blood sample analyzed with a portable coagulometer), the dosage will be adjusted. The patient's next scheduled visit will be arranged, and an additional visit will be scheduled if necessary. Adverse events will be recorded during all visits, as contained in “Adverse events” section of this protocol. During the final visit, a complete physical examination will also be performed.

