### Masking

The study is single blind, and under no circumstance does the patient know the group to which they have been assigned. The medical researchers are unaware of the randomization scheme. Although there is a risk of unmasking the patient, and the lack of masking for the physician may affect the evaluation variables, we believe that total masking is not feasible in a study using a pragmatic approach.

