### Safety procedures and monitoring of adverse events

#### Anticoagulation monitoring

The INR (International Normalized Ratio) will be determined using a portable coagulometer (CoaguCheck®, Roche FarmaSA, Madrid, SPAIN)) during the visits on days 0, 3, 7, 15, 30, 60 and 90, to verify that the patients are properly anticoagulated and to make the necessary dose adjustments. Dosing adjustments will be performed according to standard clinical practice. For the experimental group, the genetic results will also be taken into account.

If clinically necessary, additional INR measurements and visits will be performed according to standard clinical practice.

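### The INR component of the safety endpoint is counted per patient without regard to how many INRs were taken, so a between-arm difference in special INRs would appear partly as a safety difference

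*Protocol article*

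**What the plan says.** Protocol article, Assessment variables, Safety: the endpoint is the "Proportion of patients with relevant adverse events during the first three months following the start of oral anticoagulation". The listed events start with "These events include the following: INR >4 or <1.5; need for vitamin K; bleeding episode", followed by thromboembolic event, need for LMWH, infarction, stroke and death. The word 'any' is not used, but a proportion of patients implies that one qualifying INR is enough.

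Anticoagulation monitoring: INR is measured "during the visits on days 0, 3, 7, 15, 30, 60 and 90" in both arms, which makes seven scheduled INRs. The same section adds: "If clinically necessary, additional INR measurements and visits will be performed according to standard clinical practice". The footnote to Table 1 says that "additional visits can be scheduled as needed, at the discretion of the clinical researcher". No maximum is given. Study procedures: "Any changes made to the dosage and all INR measurements will be recorded in the CRF and the medical records", so the extra values reach the dataset.

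Masking: the physician is not blinded, and the article accepts that "the lack of masking for the physician may affect the evaluation variables".

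The number of special INRs is a secondary effectiveness variable, and the Discussion suggests that better control could reduce monitoring visits. The Statistical analysis section has no rule for unequal numbers of INRs in the safety endpoint.

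**The concern.** An INR excursion exists in the data only if a sample was taken on that day. A per-patient indicator of ever having been beyond 1.5 to 4 can rise, and can never fall, as samples are added. The secondary safety objective compares event frequency between the algorithm and standard practice. The decision to take an extra sample lies with someone who knows the arm, and the trial itself treats the number of extra samples as an outcome that may differ. If it does differ, two arms with the same INR behaviour can show different proportions in this component, and the more closely watched arm looks less safe. Bleeding, thromboembolism, infarction, stroke and death do not depend on an INR sample in this way, so the point concerns the INR component.

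**Working it through.** **Plan's own figures.** The article gives no rate or power for the safety endpoint. Its sample size does reproduce. For 40% against 60%, two-sided alpha 0.05 and power 80%, n = [1.96·√(2·0.5·0.5) + 0.8416·√(0.24 + 0.24)]² / 0.20² = 96.9, that is 97 per group. The present point does not affect it.

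**Inputs from the article.** Seven scheduled INRs per patient; no cap on extras; 120 patients per arm recruited. **Assumed, because the article does not give them:** the risk p that one INR is beyond 1.5 to 4 (the same in both arms), the correlation between INRs, and the number and timing of extras.

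**Step 1: independent INRs, 7 against 9.** P(at least one excursion in k INRs) = 1 − (1 − p)^k. The last column is the chance of a nominal P<0.05 against the more-sampled arm at 120 per arm, where 2.5% is expected in that direction.

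| p | 7 INRs | 9 INRs | gap (points) | false signal |
|---|---|---|---|---|
| 0.02 | 13.2% | 16.6% | 3.4 | 11% |
| 0.05 | 30.2% | 37.0% | 6.8 | 20% |
| 0.10 | 52.2% | 61.3% | 9.1 | 29% |
| 0.15 | 67.9% | 76.8% | 8.9 | 34% |
| 0.20 | 79.0% | 86.6% | 7.5 | 34% |

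**Step 2: correlated INRs.** With a correlation time of 7 to 14 days, a between-patient variance share of 0 to 0.3 and p of 0.05 to 0.15, adding two INRs (days 22 and 45) to the seven gives gaps of 3.9 points (22.7% to 26.6%) up to 9.0 points (64.6% to 73.6%). Correlation shrinks the gap but does not remove it.

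**Step 3: timing of the extras.** Simulated daily log-INR from day 7 to day 90: centre 2.45, SD 0.3, day-to-day correlation 0.9, so about 10% of INRs lie beyond 1.5 to 4. Scheduled samples are on days 7, 15, 30, 60 and 90. Days 0 and 3 are left out and there is no dose correction.

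- Scheduled INRs only: 40.6% of patients have an event.
- Two extras on random days: about 48.5%, a gap of 8 points.
- One recheck 4 or 7 days after each scheduled INR outside 2 to 3, up to day 90 (about two extras per patient): 50.8% or 49.4%, a gap of 10.2 or 8.8 points.
- The same rechecks with a 30% between-patient variance share: 37.1% rises to 45.9% or 44.9%, a gap of 8.8 or 7.8 points.
- Extras only after a scheduled INR already >4 or <1.5: 0 points, because those patients are already counted.

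**Step 4: ceiling.** If a share s of patients already has an event in both arms, independently of later INRs, the gap is multiplied by (1 − s). The 9.1 points at p = 0.10 become 4.5 (s = 0.5), 1.8 (s = 0.8), 0.5 (s = 0.95) and 0 (s = 1).

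A high s is possible for two reasons in the text. The window opens at the start of anticoagulation, on day −3 or −2, so an INR <1.5 on day 0 or day 3 counts. And need for LMWH is a listed event, while the Concomitant medication section gives LMWH to all patients for at least seven days.

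**The case against.** The strongest case against has five parts.

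- **Size.** A reader might infer a spurious gap of 8 points for two extra INRs and 14 for four (40.6% to 54.9%). The article does not support those as estimates for its endpoint. They leave out the day 0 and day 3 INRs that the definition counts, and they place extras on random days although the article ties them to dose adjustment and clinical need. This stands.
- **Dominance.** A reader might also infer that INR excursions drive the composite. No event rates are given, and the literal LMWH item could saturate it. Early INR <1.5 could saturate the INR component itself. This stands.
- **Premise.** The Discussion links fewer visits to better control. If the algorithm arm is sampled less because it is better controlled, part of a difference is real. This stands: one cannot infer that the algorithm arm will look falsely safer. Closer checking of that arm would bias the other way.
- **Strategy comparison.** In a pragmatic trial, counting every observed excursion is defensible, and dropping observed INR >4 values from a safety count is not obviously an improvement. This argues for adding an analysis, not for replacing the composite.
- **Visibility.** The number of special INRs is already compared between arms, and an analysis plan that is not shown may hold more. A count reported beside the result reveals unequal sampling but does not say how much of the safety difference comes from it. The printed definition depends on monitoring intensity whatever is written elsewhere.

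**Conclusion.** The point holds as a conditional one. As defined, the INR component depends on the number of INRs taken, that number is left to an unmasked physician without a cap, and nothing in the article separates the two effects. The article does not show that sampling will differ between arms, nor in which direction.

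For about two extra INRs per patient in one arm and the same INR behaviour in both, the gap lies between 0 and about 10 points. The lower end applies when extras follow only INRs already beyond 1.5 to 4, or when the proportion is at its ceiling. The upper end applies when rechecks follow any INR outside 2 to 3, with no ceiling and no effect of dose correction. Excursion rate, correlation, and number and timing of extras are all assumptions. The matter concerns a secondary safety comparison and leaves the primary variables and the 97 per group untouched. It is worth correcting because the correction is cheap.

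**What to change.** In Assessment variables, Safety:

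1. Keep the composite with all observed events.
2. Add a between-arm comparison of the INR component that uses only INRs from the scheduled visits, with the same days and windows in both arms.
3. In that comparison report INR >4 and INR <1.5 separately, so that low values on days 0 and 3 do not hide a difference in high values.
4. Show by arm the excursions found only at special INRs, beside the number of special INRs taken.

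The cost is wording and one extra table; all the INRs are already recorded. The added comparison has fewer events and misses excursions between visits, notably after day 30 when scheduled INRs are 30 days apart. Those excursions stay in the composite and in the listing. It also does not make the arms fully alike, because a special INR that leads to a dose change can alter the next scheduled value. That is a consequence of management, though, not of how often one looked.

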### Definition of the intervention

Once included in the clinical trial, patients will be randomly assigned to the experimental or control groups. Initially, all patients will receive treatment with low molecular weight heparins (LMWH) along with the standard acenocoumarol dose established according to age, for a maximum of three days (the time required to obtain the genotyping result). Subsequently, dose adjustment will be different in the two groups:

Patients assigned to the experimental strategy will receive the regimen determined by the pharmacogenetic algorithm, which includes demographic (age, gender, weight and height), clinical (concomitant medication) and pharmacogenetic (polymorphisms of *CYP2C9*, *VKORC1*, *APOE* and *CYP4F2*) variables
[25]. INR is also taken into account.

Patients assigned to the control strategy will receive doses according to the standard procedure in routine clinical practice.

As a guide for handling and adjusting the acenocoumarol dosages, the researchers will be referred to the local guidelines developed in ‘Area 5’ for the management of patients treated with acenocoumarol.

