Inclusion phase (days −3 or −2): After recording in the case report file (CRF) that the patient meets the selection criteria, the patient's clinical situation will be reviewed and the following information about the medical history will be recorded in the CRF: personal history and anamnesis, including concomitant medication with current dosage and regimen, and complete physical examination which will include height and weight. The patient will also be provided with a card listing basic information about the trial, what to do in the event of severe adverse events and the research team's telephone numbers. The start of the treatment with acenocoumarol will occur on day −3 or −2, according to standard clinical practice. The following dosages will be provided to the researcher as a guideline for the local recommendations: 2 mg a day for patients below 65 years of age and 1 mg a day for older patients or those with risk factors.

Pharmacogenetic specimen collection: During recruitment, a blood sample will be taken from the patient (two tubes of 5 mL EDTA K3) and will be sent by messenger to the laboratory where the patient's genotype will be determined.

The samples do not require special conservation or transportation conditions. In the event that the messenger collects the sample the day after extraction, it is recommended that the blood sample be stored in a refrigerator.

The results will be sent by email within 48 hours. The medical monitor will ensure compliance with these deadlines and will solve any logistical problems that may arise.

Individualization phase:

Day 0:

– Control group: The INR will be determined in a capillary blood sample by means of a CoaguCheck® portable coagulometer (Roche FarmaSA, Madrid, SPAIN), and the acenocoumarol dosage will be determined according to standard clinical practice.

– Intervention group: At this time, the results of the genotyping will have returned and the acenocoumarol dose will be calculated according to the developed algorithm.

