### Concomitant medication

– After the diagnosis, as recommended by international guidelines on the treatment of VTE, all patients (both the control and experimental groups) will receive low molecular weight heparins (LMWH) for at least seven days.

– All other medication that the patient is taking will be recorded in their medical history and CRF, as well as any changes they present during the course of the study. We will record the brand name of the medication, the active ingredient, dosage schedule, start or change in treatment, end of treatment and whether there has been any resolution of the problem that caused the start or change of treatment.

As is standard practice, the study's medical researchers will take into account this change in medication when adjusting the acenocoumarol dosage for both the experimental and control group.

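### The safety composite counts INR below 1.5 and need for LMWH from the first acenocoumarol dose, without exempting the planned LMWH course or the induction INRs, so start-up events shared by both arms dilute the safety comparison

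*Protocol article*

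**What the plan says.** The Safety heading under Assessment variables names one variable: "Proportion of patients with relevant adverse events during the first three months following the start of oral anticoagulation". The list reads "These events include the following: INR >4 or <1.5; need for vitamin K; bleeding episode; thromboembolic event; need for LMWH", followed by myocardial infarction, stroke and death from any cause. It has no qualifier on LMWH, on the timing of the INR, or on an induction phase.

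Other sections place routine treatment inside that window:

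- Definition of the intervention: "Initially, all patients will receive treatment with low molecular weight heparins (LMWH) along with the standard acenocoumarol dose established according to age".
- Concomitant medication: "all patients (both the control and experimental groups) will receive low molecular weight heparins (LMWH) for at least seven days".
- Study procedures: "The start of the treatment with acenocoumarol will occur on day −3 or −2, according to standard clinical practice". The algorithm dose is first calculated on day 0, when the genotype is available.
- Anticoagulation monitoring: INR is determined "during the visits on days 0, 3, 7, 15, 30, 60 and 90".
- Exclusion criteria: patients who have already had two or more acenocoumarol doses are not eligible, so participants enter untreated or nearly so.

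The first secondary objective is a between-arm comparison of how often relevant clinical events occur.

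**The concern.** An event that happens because treatment is being started, and would happen whichever arm the patient is in, carries no information about the algorithm's safety. In an any-event composite it also does harm: once a patient is an event through start-up, a later bleed, thrombosis or INR above 4 in that patient no longer changes the result.

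Two components are open to this. LMWH is planned for everyone and overlaps the first acenocoumarol doses. INR below 1.5 is assessed from day 0, after at most a few starting doses. At stake is the only safety comparison that the protocol names: real differences in later events could be hidden behind a high background rate common to both arms.

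**Working it through.** **1. The plan's own figure.** The protocol gives no sample size or event rate for the safety composite. To confirm that the formula matches the sponsor's method, take the day-7 endpoint: 40% versus 60%, alpha 0.05 (two-sided), beta 0.2, 1:1 allocation, pooled variance under the null, no continuity correction. This gives 97 per group, as stated. The recruitment target of 120 per group is used below because the main analysis includes all recruited patients.

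**2. Timeline, sections side by side.**

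| Time | What happens | Inside the safety window? | Can the algorithm have acted? |
|---|---|---|---|
| Day −3 or −2 | First acenocoumarol dose, LMWH alongside | Yes, the window opens here | No |
| Day 0 | INR measured; algorithm dose first calculated | Yes | No |
| Day 3 | INR measured | Yes | Three days of different dosing at most |
| Day 7 | INR measured; LMWH is given for at least seven days after diagnosis | Yes | Yes |

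Table 1 first ticks acenocoumarol dosing on day 0, whereas the text starts it on day −3 or −2. On the Table 1 reading, the day-0 INR could even be a pre-treatment value. On either reading it precedes any effect of the algorithm.

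**3. Dilution.** Let *f* be the share of patients in each arm who are automatic start-up events, and *p* the rate of later events. If the two are independent and *f* is equal in both arms, then

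composite rate = *f* + (1 − *f*)·*p*, and difference = (1 − *f*)·(*p*C − *p*E).

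Power = Φ[(d − 1.96·SE0)/SE1], with SE0 = √[2·p̄(1 − p̄)/n], SE1 = √[(pC(1 − pC) + pE(1 − pE))/n] and n = 120. In these expressions pC and pE are the composite rates, d their difference and p̄ their mean.

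The later-event rates of 40% (control) and 25% (experimental) are assumptions, as are all values of *f*.

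- *f* = 0: p̄ = 0.325, SE0 = 0.0605, SE1 = 0.0597, z = (0.15 − 0.1185)/0.0597 = 0.53, power 70%.
- *f* = 0.7: rates are 0.7 + 0.3 × 0.40 = 0.82 and 0.7 + 0.3 × 0.25 = 0.775. SE0 = 0.0519, SE1 = 0.0518, z = (0.045 − 0.1017)/0.0518 = −1.09, power 14%.

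| *f* | Control | Experimental | Difference (points) | Power, 120 per arm |
|---|---|---|---|---|
| 0 | 40% | 25% | 15 | 70% |
| 0.3 | 58% | 47.5% | 10.5 | 37% |
| 0.5 | 70% | 62.5% | 7.5 | 23% |
| 0.7 | 82% | 77.5% | 4.5 | 14% |
| 0.9 | 94% | 92.5% | 1.5 | 7% |

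**4. Sensitivity.** With assumed later rates of 30% versus 15%, power runs 80%, 37%, 22%, 13% and 6% over the same values of *f*. The pattern does not depend on the particular pair: 30% automatic events already cut power to about half.

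**5. Limiting case.** If the planned LMWH itself counts, *f* = 1, both arms are at 100% and the difference is zero whatever the true effect.

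**The case against.** A reader might infer that practically every patient is an event, so that the composite sits at 100% in both arms and the safety objective cannot be answered. The documents do not support that, for three reasons.

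- Need for LMWH stands beside need for vitamin K in a list of adverse events. It most naturally means unplanned LMWH, not the scheduled course. All 240 patients being events is the literal reading only. What stands is that the text does not say so. Because the planned course is open-ended ("will receive low molecular weight heparins (LMWH) for at least seven days"), it also does not show where planned treatment ends and an event begins.
- No section gives the share of patients with INR below 1.5 on any day. The assumed 40% in range on day 7 does not measure it, since the remaining 60% includes INRs between 1.5 and 2 and above 3.
- The Adverse events section records every adverse event and grades bleeding by ISTH. Bleeding, thromboembolism and death can therefore be compared separately, whatever happens to the composite.

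It is also fair to say that early under-anticoagulation may be part of the treatment effect. The Discussion stresses reaching range quickly because risk is greatest in the first weeks. That has force for days 3 and 7, when the arms are dosed differently, and there *f* need not be equal between arms. It has none for day 0.

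Last, counting windows are often left to the full protocol or analysis plan. Here, however, the article does state a window, "during the first three months following the start of oral anticoagulation", and an event list. The objection is to what those two say together, not to missing detail.

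**Conclusion.** The point holds as a flaw in a stated counting rule. The window opens at the first acenocoumarol dose, and neither the planned LMWH course nor the induction INRs are exempt. Any INR below 1.5 on day 0 is an event that the algorithm could not have influenced. Such events dilute the between-arm comparison.

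The size is not known from the documents. Under assumed later rates of 40% versus 25%, equal start-up shares in both arms and independence of early and late events, power falls from about 70% to between 37% and 14% for start-up shares of 30% to 70%. A difference of exactly zero follows only from the literal LMWH reading. Severity is moderate: the composite serves a secondary objective, the sample size and the primary variables are untouched, and the data needed for repair are collected.

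**What to change.** Before analysis, reconcile the Safety, Definition of the intervention and Concomitant medication sections:

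1. Count LMWH as an event only when it is additional to the planned initial course, and state how the end of that course is identified in the data.
2. Count INR below 1.5 only after an induction period whose end the investigators fix in advance. The documents give no basis for a particular day, so the choice is theirs, but it should exclude day 0.
3. Report the clinical events (bleeding by ISTH grade, thromboembolism, myocardial infarction, stroke, death) separately from the INR and treatment components.

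The cost is one paragraph of amendment. INR results, dose changes and concomitant-medication changes are already recorded in the CRF, so no new data are needed. The composite event rate will be lower than under the present wording. The change concerns event counting only and leaves patient management as it is.
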